### Sample Size Calculation and Statistical Analysis

We computed the required sample size with the G^*^Power 3.1.9.2 software (Faul et al., 2007; Erdfelder et al., 2009) for the *F*-test. The main endpoint will be the difference in the improvement of the overall score of the IES-R scale. A repeated measure ANOVA will be performed to test differences in the IES-R total scores between groups across the four-time points. The Type I error (α) rate was set at 0.05 (two-sided) and the Power (1 – β) was set at 0.95. The a priori correlation between repeated measures was set at 0.5 and the value of the F was set at 0.25 (*medium* effect size). We found a required sample of 132 subjects. To consider the possibility of attrition, we increased the sample by 14% of the required sample size. The total sample resulted in 150 participants (75 per group). Time will be considered a within-subjects variable, while the type of intervention will be considered a between-subject variable. *Post hoc* comparisons with the Tukey HSD-test will be performed and the effect sizes will be reported in the form of η^2^.

The same analyses will be repeated for all the questionnaires, except the one on the demographic variables. Indeed, as secondary analysis, differences in questionnaire scores between the two groups (i.e., HADS, Distress Thermometer, IES-R, Connor-Davidson Resilience Scale, the UCLA Loneliness Scale) will be assessed using the same analysis of the IES-R scale.

Group differences in questionnaires' measures will be analyzed with *T*-tests, while the chi-square statistic will be used to test the association between treatment groups and socio-demographic variables (gender, age, marital status, and employment status). Correlation analysis will be applied to assess the association between the questionnaires scores across all the time points.

Moreover, the scores of the HADS questionnaire will also be interpreted according to the clinical cutoffs (Annunziata et al., 2020). The scale score reliability (Cronbach α) will also be computed.

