## Abstract

**Background:** Cancer patients are now facing a double distinctive challenge of survival against both the disease and fear of contracting COVID-19. This challenge has resulted in the forced adoption of social distancing measures and reorganization of the delivery of medical and psychological treatments. The perceived loneliness and uncertainty increased distress and symptoms burden. In the current period, eHealth interventions might provide valuable benefits in the field of cancer care.

**Objective:** The overall goal of the study protocol will be to provide an innovative intervention for cancer patients based on an online platform, to help them manage and prevent psychological problems related to social isolation. Specifically, the efficacy of two web-based interventions aimed at lowering stress in cancer patients will be tested and compared.

**Methods:** One hundred and fifty participants (75 per group) will be enrolled in a two-group randomized trial. The two interventions will be composed either by exercises on relaxation and meditation practices, presented in both automated online content and interactive group sessions or by fixed psychoeducational online content. Stress, anxiety, and depressive symptoms, distress, resilience, and perceived social isolation will be measured before the start of the interventions (T0), 2 weeks (T1), 4 weeks (T2), and 2 months (T3) after the beginning of the interventions in both groups. A repeated measures ANOVA will be performed to test differences in the questionnaires' scores between groups across the four-time points.

**Expected Results:** We hypothesized greater improvement in the specific domain of stress symptoms (IES-R) assessed in the group receiving the interactive intervention, compared to the group which will receive only fully automated psychoeducational content. Secondarily, we expect the same trend of improvement across all the psychological variables in the blended intervention group.

**Conclusions:** Implementing these practices on people who are forced into mandatory social isolation may help them become more aware of their mind-body condition and reduce negative effects. Moreover, relaxation techniques help individuals in achieving a greater state of well-being, increasing the ability to cope with stressful situations (resilience), and strengthening the immune system.

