the Hospital Anxiety and Depression Scale (HADS) (Zigmond and Snaith, 1983) for assessing anxiety and depressive symptoms. It is a 14-items scale divided into two subscales ranging from 0 (not at all) to 3 (high presence of symptoms), with higher values indicating higher levels of anxiety and/or depression;the Distress Thermometer for measuring distress symptoms (Jacobsen et al., 2005; Donovan et al., 2014). It is a single-item tool with a Likert scale ranging from 0 (no distress) to 10 (extreme distress);the Impact of Event Scale-Revised version (IES-R) (Weiss, 2007) for assessing the reflect intrusion (eight items), avoidance (eight items), and hyperarousal (six items) related to traumatic events. It is a 22-item scale ranging from 0 (not at all) to 4 (extremely), with a higher score indicating higher distress in response to a specific traumatic event;the Connor-Davidson Resilience Scale (Connor and Davidson, 2003) for measuring the resilience level of cancer patients. It contains 25 items ranging from 1 to 5, with higher scores indicating higher resilience;the UCLA Loneliness Scale (Version 3) (Russell, 1996) for assessing social loneliness. It consists of 20-items ranging from 1 (Never) to 4 (Often), with a higher score indicating greater feelings of loneliness and social isolation.

All the previous questionnaires will be administered before the start of the interventions (T0). Two weeks (T1), 4 weeks (T2), and 2 months (T3) after the beginning of the interventions, participants will be asked to complete the same questionnaires.

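### The primary 2 × 4 ANOVA counts pre-treatment T0 as an outcome, does not adjust for it, and does not say which F-test decides a difference in improvement

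*Protocol article*

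**What the plan says.** All of the following is in the protocol article.

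- **Endpoint** (Sample Size Calculation and Statistical Analysis): "The main endpoint will be the difference in the improvement of the overall score of the IES-R scale".
- **Hypothesis** (Abstract): "We hypothesized greater improvement in the specific domain of stress symptoms (IES-R) assessed in the group receiving the interactive intervention", compared with the fully automated psychoeducational arm.
- **Analysis** (same section as the endpoint): "A repeated measure ANOVA will be performed to test differences in the IES-R total scores between groups across the four-time points". The factors are set out as follows: "Time will be considered a within-subjects variable, while the type of intervention will be considered a between-subject variable". Tukey HSD comparisons follow, and the same analysis is repeated for every other questionnaire. No baseline covariate, primary visit or decisive F-term is named.
- **Visits** (Study Design and Measures): T0 is taken before either intervention begins; the other three come "Two weeks (T1), 4 weeks (T2), and 2 months (T3) after the beginning of the interventions".
- **Sample size inputs**: a two-sided α of 0.05, 95% power, a correlation of 0.5 between repeated measures and an effect size f of 0.25. The result is 132, raised by 14% to 150 (75 per group).

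**The concern.** A two-group, four-visit ANOVA offers two terms that could answer the primary question.

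- **Group main effect.** This compares the arms on the mean of all four visits. One of the four was measured before anyone was treated, so under randomisation it contributes noise and no expected effect. The term is not a measure of improvement.
- **Group-by-time interaction.** This does measure differential change, with T0 as part of the comparison. It has 3 degrees of freedom and responds to any non-parallel pattern, including one that favours the control arm.

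The endpoint wording points to the interaction. The sample size arithmetic points to the main effect. Nothing in the text settles which one decides. At stake are the claimed 95% power and a clear rule for declaring the trial positive. The same model is carried over to all the secondary scales.

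**Working it through.** **Inputs.** From the protocol article: two groups, m = 4 visits, α = 0.05, correlation ρ = 0.5, f = 0.25 (for two equal groups d = 2f = 0.5), N = 132, enrolled N = 150. Assumed here: SD 1, equal correlation between all visits, expected T0 difference of zero because of randomisation, and the effect profiles named below. Power is from the noncentral F distribution.

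**1. Reproducing 132.**
- Group main effect: λ = f²·N·m / [1 + (m − 1)ρ] = 0.0625 × 132 × 4 / 2.5 = 13.2, with 1 and 130 df. Power is 0.950, so 132 is matched exactly.
- Interaction: λ = f²·N·m / (1 − ρ). N = 36 already suffices (0.0625 × 36 × 4 / 0.5 = 18.0, power 0.952). The alternative (SPSS-type) effect-size convention gives 96.
- Of the terms tried, only the main effect gives 132. Then 132 × 1.14 = 150.5, consistent with 150.

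**2. What f = 0.25 implies for the main effect.** With no difference at T0, a four-visit mean difference of 0.5 needs 0.5 × 4/3 = 0.667 SD at each of T1, T2 and T3.

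**3. Power if d = 0.5 at T1, T2 and T3 and 0 at T0.**
- Main effect: mean difference 0.375; variance of the four-visit mean (1 + 3ρ)/4 = 0.625. λ = (132/4) × 0.375² / 0.625 = 7.43, power **0.77**. At N = 150, λ = 8.44, power **0.82**.
- Interaction: Σ(d_t − 0.375)² = 0.375² + 3 × 0.125² = 0.1875. λ = 33 × 0.1875 / 0.5 = 12.4, with 3 and 390 df, power **0.85**.
- T1–T3 average adjusted for T0: residual variance (1 + 2ρ)/3 − ρ² = 0.4167. λ = 33 × 0.25 / 0.4167 = 19.8, power **0.993**.
- One visit adjusted for T0: residual variance 1 − ρ² = 0.75. λ = 33 × 0.25 / 0.75 = 11.0, power **0.91**.

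**4. Dependence on the effect profile (N = 132, ρ = 0.5).**

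| Profile, d = 0.5 at its maximum | Interaction | T0-adjusted T1–T3 average |
|---|---|---|
| Sustained at T1, T2, T3 | 0.85 | 0.993 |
| Linear rise over actual weeks to T3 (2 months taken as 8.7 weeks) | 0.71 | 0.70 |
| At two of the three visits only | 0.94 | 0.84 |
| At T3 only | 0.85 | 0.31 |

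A T0-adjusted contrast at a single visit has power 0.91 whenever d = 0.5 holds at that visit, whatever happens at the others.

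**5. Two tests.** If a significant result on either term counted as success, and the two were independent, the null rate would be 1 − 0.95² = 0.0975. Simulated null trials with 75 per arm and ρ = 0.5 give 0.094 to 0.098.

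**The case against.** The strongest reply is that a repeated-measures ANOVA is a standard, valid analysis of a randomised trial. The endpoint wording identifies the interaction as the relevant term. In that term T0 is the reference for change, so baseline is used. Tukey comparisons would show direction, and further model detail belongs in an analysis plan that is not shown.

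Much of this stands. The ANOVA is not biased under randomisation, and counting T0 as an outcome harms the main effect, not the validity of the interaction. What does not fall away is the mismatch. The article itself fixes the model, factors, follow-up test and sample size, yet the sample size matches a term that does not measure improvement. Tukey comparisons are follow-up and do not supply the missing decision rule.

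Four stronger readings are tempting, and the document does not support them.

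- **A baseline-adjusted contrast always has far more power.** This holds for a sustained effect, a profile the article never states. The table shows a tie for a gradual rise and clear losses for partial or late effects.
- **The trial's false-positive rate is doubled.** The figure of about 0.10 applies only if either test may be claimed, and the article does not say so.
- **Unequal visit spacing makes the interaction test anti-conservative.** That needs an assumed decay in correlation and the absence of any epsilon correction. The article states a single correlation of 0.5 and does not rule a correction out.
- **Reporting η² hides direction.** This is minor, since α is two-sided and cell means will be compared.

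**Conclusion.** The point holds as a mis-targeted and under-specified primary test, not as an invalid analysis. The group main effect, the only term tried that reproduces 132, has power 0.77 at N = 132 and 0.82 at N = 150 for a 0.5 SD difference confined to T1–T3; the plan claims 0.95. To reach 0.95 at N = 132 it needs 0.667 SD at every post-baseline visit. The interaction answers the right question but has power 0.85 at N = 132 for the same effect, and a significant result would not by itself show greater improvement in the blended arm.

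These figures rest on the article's own ρ = 0.5 and f = 0.25, on equal correlations and on the assumed sustained effect. Missing data and clustering by group session were not modelled. That the sample size was computed for the main effect is inferred from the exact match; the article does not say which F-test option was used.

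**What to change.** Make the primary analysis a model of IES-R total at T1, T2 and T3 with arm, time, arm-by-time and T0 IES-R as terms. Name one decisive arm contrast before outcomes are seen: either one stated visit, or the T1–T3 average if a sustained effect is expected, with the reason for the choice. Report it as an adjusted mean difference in IES-R points with a 95% confidence interval. Treat the other visits and the arm-by-time test as supportive. Use the same model for the secondary scales, and restate the power for the chosen contrast.

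The cost is wording, a little more modelling and a revised power statement; no extra data or participants are needed. The real price is commitment. A contrast that does not fit the effect profile loses power: the T1–T3 average falls to 0.31 if the effect appears only at T3, and a single-visit contrast misses an effect that is absent at that visit.

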### Expected Results

We primarily hypothesize a greater improvement in the specific domain of stress symptoms (IES-R) assessed in the group receiving the interactive intervention, compared to the group which will receive only fully automated psychoeducational contents. Secondarily, we expect the same trend of improvement across all the psychological variables in the blended intervention group. Finally, we expect that the blended approach characterized by the presence of both interactive group and relaxation exercises will lead to a relief of the perceived social isolation.

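### The 132 subjects at 95% power match the group main effect averaged over T0 to T3, so 95% power is not shown for the stated endpoint, the difference in improvement

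*Protocol article*

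**What the plan says.** All the inputs stand in the Protocol article, under Sample Size Calculation and Statistical Analysis.

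- Endpoint: "The main endpoint will be the difference in the improvement of the overall score of the IES-R scale".
- Analysis: "A repeated measure ANOVA will be performed to test differences in the IES-R total scores between groups across the four-time points". Time is the within-subjects factor and intervention the between-subjects factor. The ANOVA term that decides the trial is not named.
- Sample size: G*Power, with the method given only as an F-test, a two-sided alpha of 0.05 and 95% power. On the remaining two inputs the text reads: "The a priori correlation between repeated measures was set at 0.5 and the value of the F was set at 0.25". The result: "We found a required sample of 132 subjects", raised to 150 for attrition.

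Expected Results repeats the direction of the endpoint: "We primarily hypothesize a greater improvement in the specific domain of stress symptoms (IES-R) assessed in the group receiving the interactive intervention". Study Design and Measures places T0 before the interventions start and T1, T2 and T3 after it, so the four time points in the ANOVA include one pre-intervention measurement.

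**The concern.** A two-group, four-occasion repeated measures ANOVA offers two tests that involve treatment. The group main effect compares the groups' means averaged over all occasions. The group-by-time interaction asks whether the groups change differently. Only the second speaks to improvement. A sample size computed for the first carries its power statement to the second only by coincidence.

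Two things are at stake. First, a reader takes 95% power as a property of the primary hypothesis. If it belongs to another term, the power for that hypothesis has not been stated. Second, with the deciding term unnamed, a significant main effect could later be reported as greater improvement although it does not measure improvement.

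**Working it through.** **Inputs.** From the article: k = 2 groups, m = 4 occasions, f = 0.25, correlation ρ = 0.5, alpha 0.05, power 0.95. Power comes from the noncentral F distribution with noncentrality λ. Sphericity is assumed, and N is rounded up to equal groups.

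**1. Reproducing 132: group main effect (between factors).**
λ = f²·N·m / (1 + (m−1)ρ) = 0.0625 × 4N / 2.5 = 0.1N, with df 1 and N−2.
- N = 130: λ = 13.0, power 0.947.
- N = 132: λ = 13.2, power 0.9501.

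The smallest even N is 132, an exact match. The same test gives 142 with m = 3 and 158 with m = 2, so 132 depends on averaging over all four occasions, T0 included.

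**2. Group-by-time interaction, same inputs.**
λ = f²·N·m / (1−ρ) = 0.0625 × 4N / 0.5 = 0.5N, with df 3 and 3(N−2).
- N = 36: λ = 18, power 0.952.

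The required N is therefore 36 under G*Power's default effect-size definition. Its other definitions of f give 96 (as in SPSS) and 94 (as in Cohen), and a multivariate test gives about 282. None gives 132.

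**3. What f = 0.25 means for the main effect.** With two equal groups f is half the standardised difference, so f = 0.25 is 0.5 SD averaged over T0 to T3. Randomised groups are expected to be equal at T0. A constant post-baseline difference δ must then satisfy 3δ/4 = 0.5, so δ = 0.67 SD at each of T1, T2 and T3.

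**4. Power for stated patterns of group difference.** The patterns are assumptions, because the article gives none. With d the vector of differences in SD units at T0 to T3:
- main effect: λ = (N/4)·mean(d)²·m / (1 + (m−1)ρ)
- interaction: λ = (N/4)·Σ(d − mean d)² / (1−ρ)

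For d = (0, 0.5, 0.5, 0.5) and N = 132, mean d = 0.375 and Σ(d − mean d)² = 0.1875. The main effect has λ = 33 × 0.140625 × 4 / 2.5 = 7.425. The interaction has λ = 33 × 0.1875 / 0.5 = 12.375.

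| Difference at T0, T1, T2, T3 (SD) | Main effect | Interaction |
|---|---|---|
| 0.5, 0.5, 0.5, 0.5 | 0.95 | 0.05 |
| 0, 0.67, 0.67, 0.67 | 0.95 | 0.98 |
| 0, 0.5, 0.5, 0.5 | 0.77 | 0.85 |
| 0, 0.25, 0.5, 0.5 | 0.62 | 0.81 |

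(N = 132, ρ = 0.5.) The first row has no difference in improvement at all, yet the main effect is detected with 95% power. If all 150 are analysed, the third row becomes 0.82 and 0.89.

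**5. Sensitivity to ρ.** For (0, 0.5, 0.5, 0.5) and N = 132, interaction power is 0.70 at ρ = 0.3, 0.85 at 0.5, 0.95 at 0.65 and 0.98 at 0.7. Main-effect power moves the other way: 0.87, 0.77, 0.70 and 0.68.

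**6. Baseline-adjusted contrast, for reference.** This is not the planned analysis. The residual variance after adjusting for T0 is (1+2ρ)/3 − ρ² = 0.4167 for the T1 to T3 average and 1 − ρ² = 0.75 for a single occasion (in SD² units, ρ = 0.5). With 3.605 as the sum of the normal quantiles for two-sided alpha 0.05 and power 0.95, the detectable differences at N = 132 are:
- T1 to T3 average: 3.605 × √(4 × 0.4167/132) = 0.41 SD
- single occasion: 3.605 × √(4 × 0.75/132) = 0.54 SD

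**The case against.** The strongest reply is that no shortfall has been shown. The article states its effect only as f = 0.25, never as 0.5 SD after baseline. At f = 0.25 and N = 132 the main effect has power 0.9501, and the interaction under the default definition has power above 0.999. If f = 0.25 is translated into 0.67 SD at each post-baseline visit, the interaction still has 0.98. The figures 0.77 and 0.85 belong to a smaller effect (main-effect f = 0.1875, interaction f = 0.108) at one value of ρ. This stands. A reader might infer that the trial is underpowered, or that neither ANOVA test reaches 95% at the planned effect. The document supports neither inference.

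It also stands that the G*Power procedure is an inference, since the text names only an F-test and a condensed article may leave the option to the full protocol. There is no arithmetic slip either: 132 is a correct answer to the question that was apparently put to the software.

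The reply does not remove the mismatch. The article itself prints the endpoint, the inputs and the resulting N, and these fit together only for a term that does not measure improvement. That the interaction needs anywhere from 36 to about 282, depending on how f is defined, shows that f = 0.25 alone does not fix the power for the endpoint.

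**Conclusion.** The point holds as a mismatch between the powered term and the endpoint. On the exact match, 132 subjects and 95% power belong to the group main effect averaged over T0 to T3. The endpoint and the primary hypothesis concern change. The 95% is therefore not shown for the primary hypothesis.

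The size depends on the effect that the sponsor has in mind. With a constant post-baseline difference, ρ = 0.5 and 132 analysed, interaction power is 0.98 at 0.67 SD and 0.85 at 0.5 SD, and the latter ranges from 0.70 to 0.98 as ρ goes from 0.3 to 0.7. Whether 132 to 150 is enough is left open until the effect is stated for the right term. The conclusion rests on the inferred procedure, equal expected means at T0 by randomisation, a common SD and correlation across occasions, and the assumed patterns of difference.

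**What to change.** 1. Name one primary test that matches the endpoint: the group-by-time interaction, or a single pre-specified change or baseline-adjusted contrast. State that the group main effect over T0 to T3 is not the primary test.
2. Replace the sample size paragraph with the power of 132 to 150 analysed patients for that term. Give the effect in SD or IES-R points at each visit, name the procedure, and show a range of ρ in place of 0.5 alone.
3. If a baseline-adjusted analysis is preferred, say so as a change to the planned ANOVA. At ρ = 0.5, 132 analysed patients then give 95% power for about 0.41 SD on the T1 to T3 average, or 0.54 SD at one time point.

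The cost is one rewritten paragraph if the ANOVA is kept, and a change to the primary analysis as well if step 3 is taken. The restatement itself adds no patients. The stated power may become less favourable than 95%, and the choice should be fixed before outcome data are seen.

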## Materials and Methods

### Participants and Procedure

Participants will be enrolled through email. Those who will accept to take part in the study will be asked for the signature of the informed written consent. The study will receive ethical approval of the Ethical Committee of the University of the last author of the work. Then, participants will be randomly assigned to one of the two groups. In both groups, participants will receive on their email an invitation for an online platform where they will access the material. Participants will receive weekly reminders via e-mail.

A total of 150 participants (75 per group) will be enrolled based on the following inclusion criteria: (1) cancer patients (illness stage I–II); (2) aged from 18 to 65 years; (3) having an internet connection at home; (4) having a sufficient physical ability (auditory and visual ability) to use a remote internet device; (5) being a proficient Italian speaker; (6) providing the written informed consent. Patients (1) with neurological or psychiatric diseases, (2) hospitalized, and (3) with expertise in relaxation techniques or meditation will be excluded from the study.

Participation in the study will be voluntary, and participants will be allowed to withdraw from the study at any moment. The research protocol follows the CONSORT-EHEALTH V1.6 Guidelines (Eysenbach and CONSORT-EHEALTH Group, 2011). The study will be conducted according to the principles stated in the Declaration of Helsinki (59th WMA General Assembly, World Medical Association, 2008).

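### The named four-wave ANOVA in its standard form uses only participants with all four IES-R scores, and the increase to 150 covers just 12% of participants missing any wave

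*Protocol article*

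**What the plan says.** All of this is in the protocol article.

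- **Primary analysis** (Sample Size Calculation and Statistical Analysis): "A repeated measure ANOVA will be performed to test differences in the IES-R total scores between groups across the four-time points". The factors are fixed as follows: "Time will be considered a within-subjects variable, while the type of intervention will be considered a between-subject variable".
- **Endpoint** (same section): "The main endpoint will be the difference in the improvement of the overall score of the IES-R scale".
- **Sample size** (same section): alpha is 0.05 and power "was set at 0.95". "The a priori correlation between repeated measures was set at 0.5 and the value of the F was set at 0.25". The result is 132.
- **Attrition** (same section): "To consider the possibility of attrition, we increased the sample by 14% of the required sample size". The total is 150, 75 per group.
- **Withdrawal** (Participants and Procedure): "participants will be allowed to withdraw from the study at any moment".
- **Waves** (Study Design and Measures): the questionnaires are completed at T0 and again at 2 weeks, 4 weeks and 2 months.

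The article states no expected dropout rate and no rule for incomplete participants. The secondary scales get the same analysis as the IES-R.

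**The concern.** A classical repeated-measures ANOVA works on one row per participant with every wave filled. One missed questionnaire then removes that person's other three scores as well. The loss that matters is therefore the share of participants missing any of T1, T2 or T3, which is larger than the share missing a given wave.

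Two things are at stake. The first is power, because scores that were collected go unused. The second is the comparison itself, if those who fail to complete differ between arms in a way related to stress. The arms do differ in burden: the blended arm has a scheduled weekly 45-minute group session plus audio and video twice a week, while the control arm receives links three times a week. The article's own Discussion says that engagement with the group sessions may depend on participants' attitude.

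**Working it through.** **1. The plan's figure.** Inputs from the sample size section: f = 0.25, m = 4 waves, rho = 0.5, two groups, alpha = 0.05, power 0.95. For the between-group test of a repeated-measures ANOVA:

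lambda = f² × N × m / (1 + (m − 1) × rho) = 0.0625 × N × 4 / 2.5 = 0.1 × N, with 1 and N − 2 degrees of freedom.

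At N = 132, lambda = 13.2 and power is 0.9501. The stated 132 reproduces, and it counts participants with all four waves.

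**2. The margin.** 132 × 1.14 = 150.5, reported as 150. The loss that still leaves 132 is 1 − 132/150 = 12.0%, or 18 people. A 14% loss would leave 150 × 0.86 = 129 (power 0.946); covering it in full would need 132/0.86 = 153.5, so 154.

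**3. Per-wave equivalent.** Assume T0 is complete and misses at T1 to T3 are independent with probability p. Complete cases are 150 × (1 − p)³. Setting (1 − p)³ = 0.88 gives p = 4.2%.

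| Assumed p per wave | Complete cases | Power at that N |
|---|---|---|
| 4.2% | 132 | 0.950 |
| 5% | 150 × 0.857 = 128.6, about 129 | 0.946 |
| 10% | 150 × 0.729 = 109.4, about 109 | 0.905 |
| 15% | 150 × 0.614 = 92.1, about 92 | 0.851 |

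**4. Bias.** Simulation with no true effect, 75 per arm and rho = 0.5, analysing four-wave completers. All dropout settings are assumptions. In rows 3 to 6, dropout follows T1. "Slope" is the logistic coefficient of dropout on the T1 score.

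| Assumed missingness | Bias in group difference averaged over waves | Type I error of that test |
|---|---|---|
| 10% random per wave, both arms | about 0 | about 5% |
| Related to the preceding score, same rate and mechanism in both arms | about 0 | about 5% |
| 20% blended, 8% control, both random | about 0 | about 5% |
| 20% blended, 8% control, slope 1.0 in both | 0.06 SD | about 7% |
| 20% blended with slope 1.0, 8% control random | 0.11 SD | about 12% |
| 25% blended with slope 1.5, 8% control random | 0.17 SD | about 23% |

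In the last three rows the bias favours the blended arm, because its more stressed participants leave more often.

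**5. The effect measured.** The biases above concern the group effect averaged over all four waves including T0, which is the test that reproduces 132. In the last two scenarios the T0-to-T3 change is biased by 0.002 SD or less. With equal correlations, selection on T1 shifts T0 and T3 alike. The type I error of the group-by-time F-test there is about 7% and 10%.

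**6. The alternative.** A likelihood-type estimator using every observed wave had bias of about 0.00 in the last two scenarios, because the T1 score that drives dropout stays in the analysis.

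**The case against.** Several objections stand.

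- **The 14% is not an arithmetic error.** The article says the sample was increased by 14% of 132, and it was, to rounding. It does not say that 14% loss is expected or covered. A reader might infer a miscalculated allowance, but the text does not support that. Even if 14% loss was meant, the shortfall is 4 people and about 0.4 points of power.
- **No complete-case rule is written.** Dropping incomplete participants is the usual behaviour of the named method, not a stated rule. Imputation, sensitivity analyses and continued follow-up of people who stop the intervention may be set out in a full protocol or analysis plan that is not shown. Their absence here is no finding.
- **The sample is not broken.** Power for the between-group test is still 0.930 at 120 completers and 0.903 at 108 (28% loss).
- **Ordinary missed questionnaires do not bias the comparison.** A reader might infer that any incomplete follow-up does. The first three scenarios show otherwise: bias needs dropout that is related to the outcome and also differs between arms.
- **The larger bias figures depend on chosen assumptions.** They make dropout stress-related in one arm and random in the other, which no part of the article establishes. They also concern the averaged group effect, whereas the stated endpoint is improvement.

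What remains is a criticism of a method the article does fix. A mixed model on all observed waves is a different primary analysis from the one named, so the point does not depend on text that is missing.

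**Conclusion.** The point holds in limited form, as a recommended change to the analysis. The standard form of the named ANOVA ties the primary analysis to four-wave completers, and the margin for losing them is 12% in total. The stated power of 0.95 is then missed under modest assumed miss rates, but by a few points and not by a collapse.

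Bias is a risk and not a demonstrated consequence. The difference in burden makes arm-specific, outcome-related dropout plausible. Its assumed size is 0.06 to 0.17 SD on the averaged group effect, with no material bias in the T0-to-T3 change where that was examined. The conclusion rests on the standard behaviour of the method, on independent misses for the per-wave figures, and on rho = 0.5 with the dropout models listed for the bias figures.

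**What to change.** Make the primary analysis a likelihood-based mixed model that uses every observed T1 to T3 IES-R score of all randomised participants in their assigned arm, with T0 as covariate. Apply the same model to the secondary scales. State that the increase from 132 to 150 covers 12% loss of complete four-wave cases.

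The cost is a small change of analysis wording, with no extra participants, visits or measures. The model relies on data being missing at random given the observed scores. A participant with no follow-up score at all still adds no outcome information.
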